### Primary outcome

Along with the primary objective, the primary study outcome will be the unadjusted mean differences between different management groups of each individual mental wellbeing outcome at 3-, 6-, 9- and 12-months post diagnosis. For this a one-way ANOVA between treatment groups, is planned at each time frame. Subsequent Tukey’s Honest Significant Difference post-hoc analysis will be conducted on any means identified to be statistically significantly different.

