## Study aims

With the current literature deficiencies and limited existing evidence on prognostic factors for mental wellbeing outcomes in prostate cancer, the proposed study is primarily aimed as an exploratory study to further define potential factors of interest [19]. Therefore, the primary aim of the study is to evaluate the association between prostate cancer patients undergoing different management options and subsequent mental wellbeing outcomes in the initial cancer follow-up stage. We hypothesise there to be significant differences between different management groups in view of their varying physical symptom loads and demands. More specifically, that those undergoing hormone monotherapy possess the poorest mental wellbeing outcomes, with those undergoing active surveillance the least.

In addition to this, secondary aims include:

To explore patient and oncological prognostic factors associated with mental wellbeing outcomes in patients with prostate cancer.Define incidence of individual mental wellbeing issues in the first year after diagnosis.Explore trajectory of mental wellbeing symptoms in the first year after diagnosis.Assess the relationship between mental wellbeing symptoms and functional, social wellbeing and general health outcomes.

We hypothesise that several patient factors including age, previous mental health history and comorbidities will be significant prognostic factors for poorer mental wellbeing outcomes, based on existing literature in other cancer groups. Similarly, we hypothesise that oncological factors such as stage at presentation and time since diagnosis will be significantly associated with mental wellbeing. Specifically, for time since diagnosis/ symptom trajectory, we hypothesise a downward trend of symptom severity for symptoms such as depression, anxiety and FCR due to increasing time since original diagnosis and reduced uncertainty present post treatment, whilst an upwards trajectory for body image and masculinity symptoms is expected as treatment related side-effects begin to increase with time. Lastly, in view of the extensive literature linking mind and body outcomes in various urological conditions, we believe those with significant mental wellbeing symptoms will possess poorer functional outcomes at study conclusion.

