### Sample size

Target sample size calculations are based on the primary aim and outcome of the study evaluating mean differences between different treatment cohorts. This was conducted for hypothesis testing against minimal clinically significant difference (MCSD) of the five mental wellbeing measures of interest, as previously reported in the literature. This was calculated utilising a one-way ANOVA across the four cohorts. Common standard deviation (SD) derived from the literature, or previous pilot data from a small cross-sectional sample were also used to subsequently calculate the effect size f value, with a power of 0.8 and an alpha value of 0.05 utilised. G*Power Software V3.1 [30] was used to calculate the required sample sizes. The largest required sample size across the five mental wellbeing measures was used as the required minimal sample size.

PHQ-9 –MCSD of 5 [31], SD of 3.49 (pilot data)GAD 7 –MCSD of 5 [32], SD of 3.49 (pilot data)FCR7 –MCSD of 10, SD 7.01 [24]BIS–No clear MCSD published in literature [33], use of 10 as cut off for significant symptoms [25], SD of 3.93 (pilot data)Masculine Self-Esteem MCSD of 9.8 [34], SD of 15.79 [35]

Sample size calculations utilising the above values revealed a maximum requirement of 232 participants (58 per cohort) using the PC-QOL Masculine Self-Esteem Scale. Assuming a reasonable dropout rate of 25%, a requirement of 75 participants per cohort was set to give an overall target sample of 300 participants. During recruitment, individual treatment cohorts of these sizes will be targeted, with a gradual stop in recruitment across these different cohorts to gain sizes of groups as close to equal as possible. However, due to likely unequal dropout rates and some crossover to different treatment arms during follow up (e.g. those undergoing surveillance subsequently undergoing radical treatment) it is likely some disparity in cohort sizes will exist. These would subsequently require consideration within analysis and conclusions drawn from study results if any individual cohort contains fewer than the minimum sample size described above.

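### Pairwise differences are the primary outcome but are analysed only after a significant ANOVA, so a null result that would exclude the MCSD on PHQ-9, GAD-7 or FCR7 is not produced

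*Protocol article*

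**What the plan says.** The Primary outcome section defines the target as a set of differences: "the primary study outcome will be the unadjusted mean differences between different management groups of each individual mental wellbeing outcome", at 3, 6, 9 and 12 months. The test is then fixed: "For this a one-way ANOVA between treatment groups, is planned at each time frame". The pairwise step follows only on significance: "Subsequent Tukey’s Honest Significant Difference post-hoc analysis will be conducted on any means identified to be statistically significantly different". No clinical threshold appears in that section.

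The Sample size section gives an MCSD for four scales: PHQ-9 5, GAD-7 5, FCR7 10 and masculine self-esteem 9.8. For the Body Image Scale (BIS) it reports that no clear MCSD is published and enters a symptom cut-off of 10 instead. It describes the sizing in these words: "This was conducted for hypothesis testing against minimal clinically significant difference (MCSD) of the five mental wellbeing measures of interest". It adds: "This was calculated utilising a one-way ANOVA across the four cohorts", "with a power of 0.8 and an alpha value of 0.05 utilised". The choice among scales is explicit: "The largest required sample size across the five mental wellbeing measures was used as the required minimal sample size". The result is 232 participants, 58 per cohort, from masculine self-esteem.

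The hypothesis in Study aims is worded in terms of significance: "We hypothesise there to be significant differences between different management groups in view of their varying physical symptom loads and demands".

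**The concern.** Two features combine. First, the pairwise analysis of the primary outcome depends on the F test. Second, one scale sets the cohort size, so the other scales carry many more participants than their own MCSD requires.

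On PHQ-9, GAD-7 and FCR7 this works in both directions. A significant result can come from a difference well below the MCSD, and nothing in the primary analysis sets it beside that figure. A non-significant F ends the analysis of that scale and visit as described, although the same data would often show that no pair of cohorts differs by as much as the MCSD. That second finding is informative for a study of which treatment groups fare worse, and the written rule does not produce it.

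**Working it through.** **Inputs (Sample size section).** Four cohorts, alpha 0.05, power 0.80. MCSD/SD: PHQ-9 and GAD-7 5/3.49; FCR7 10/7.01; masculine self-esteem 9.8/15.79. BIS is left out because its entered value is not an MCSD. The article does not give the pattern of means, so I assume two cohorts one MCSD apart and two midway.

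**1. The plan's own figure.** Under that pattern f = (MCSD/SD)/√8. For masculine self-esteem f = (9.8/15.79)/√8 = 0.219. The noncentral F gives 58 per cohort (232) with power 0.803, which matches exactly. For PHQ-9 and GAD-7 f = (5/3.49)/√8 = 0.507, and for FCR7 f = (10/7.01)/√8 = 0.504. Each needs 12 per cohort (48).

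**2. Smallest Tukey-significant observed difference at 58 per cohort.** HSD = q(0.95; 4, 228) × SD/√58, with q = 3.660.

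| Scale | HSD | MCSD | HSD/MCSD |
|---|---|---|---|
| PHQ-9, GAD-7 | 1.68 | 5 | 0.34 |
| FCR7 | 3.37 | 10 | 0.34 |
| Masculine self-esteem | 7.59 | 9.8 | 0.77 |

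At 56 per cohort (75 less 25%) the share is 0.34 on the first three scales; at 75 it is 0.29 to 0.30.

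**3. What a non-significant F implies.** The critical F(3, 228) is 2.644. For a given F, the range of means is widest when two cohorts lie midway, so a non-significant F caps the observed range at SD × √(6 × 2.644/58) = 0.523 × SD. The simultaneous interval for the widest pair then reaches at most 0.523 × SD + 3.660 × SD/√58 = 1.004 × SD.

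- PHQ-9 and GAD-7: 1.004 × 3.49 = 3.50, below 5.
- FCR7: 1.004 × 7.01 = 7.04, below 10.
- Masculine self-esteem: 1.004 × 15.79 = 15.85, above 9.8.

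So if the observed pooled SD is near its planning value, every non-significant F on the first three scales comes with intervals that exclude the MCSD. On masculine self-esteem it need not. For PHQ-9 and GAD-7 this certainty holds up to a pooled SD of 5/1.004 = 4.98.

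**4. How often (simulation, PHQ-9, 58 per cohort).**

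- Equal true means, SD 3.49: F non-significant and all six intervals inside ±5 in about 95% of trials.
- Equal true means, SD 6 (assumed, as a sensitivity value): all six intervals inside ±5 in about 77%.
- True means 0, 1.25, 1.25, 2.5, SD 3.49: F significant in 91%, and in about 81% of all trials F is significant while every interval excludes 5 points. At 56 per cohort this is 78%; at 75 it is 93%.

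**The case against.** A reader might infer that the two sections conflict, because the sizing is described as testing against the MCSD while the analysis tests equality. The article does not support that. It names a one-way ANOVA in both places, and an ordinary zero-null F test reproduces 232 exactly. The MCSD is the alternative used for power, and sizing at the MCSD while testing zero is normal practice.

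A reader might also infer that any non-zero difference counts, or that differences of a third of the MCSD will be reported as important. Neither holds. A significant F and then Tukey significance are both required. One third of the MCSD is a threshold for an observed difference: when the true difference is that size, a given pair is flagged only about 46% to 49% of the time at 58 per cohort. The article nowhere equates significance with clinical importance, and it calls the study exploratory.

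It can also be said that intervals and their interpretation belong in a statistical analysis plan, and that mean differences could be tabulated whatever F shows. This stands in part: the article does not forbid such reporting. But the condition on the pairwise analysis is a stated rule, and it sits awkwardly with a primary outcome that consists of those differences.

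Finally, a stricter rule is tempting: claim a difference only if the estimate reaches the MCSD. That would be costly. At a true 9.8-point difference on masculine self-esteem, it would cut the chance of a positive claim from about 81% to just over half.

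**Conclusion.** The concern holds as a point about an unnecessary condition and an unused yardstick, not as an error in the sizing or a contradiction. On PHQ-9, GAD-7 and FCR7 an observed difference of about a third of the MCSD is enough for Tukey significance. With no true difference on PHQ-9, about 95% of trials would end in a bare non-significant F where intervals would have excluded the MCSD.

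These figures assume equal cohorts of 58, a common SD and the planning SDs. The PHQ-9 and GAD-7 SDs come from a small pilot, and the 95% falls to about 77% if the SD is 6. The gain does not carry over to masculine self-esteem, where the half-width of 7.59 leaves only 9.8 − 7.59 = 2.21 points of room. Any statement that the MCSD is excluded concerns an unadjusted difference between non-randomised groups.

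**What to change.** In the Primary outcome section, replace the conditional step with wording such as: For each scale and visit, all six pairwise mean differences will be reported with Tukey simultaneous 95% confidence intervals, whatever the result of the ANOVA, which remains the global test. The intervals will be shown beside the MCSDs in the Sample size section (none for BIS), and the report will say where they exclude an unadjusted difference as large as the MCSD.

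Tukey's procedure needs no preceding F test to control the family-wise error within a scale and visit, so dropping the condition costs nothing there. Do not require the point estimate to reach the MCSD before a difference is claimed.

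The cost is wording and table space: 6 pairs × 5 scales × 4 visits = 120 intervals, which can go in a supplement. No new data, participants or change to the sample size are needed.

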### Secondary outcomes

The following outcomes are not accounted for within the sample size calculations and are therefore considered exploratory. Each planned analysis will be divided per secondary aim of the study.

For exploration of prognostic factors of mental wellbeing outcomes, baseline patient, oncological and treatment factors previously described will be evaluated against the binary outcome of the development of significant individual mental wellbeing symptoms during study follow up. For this analysis an initial univariable, followed by a multivariable regression analysis of potentially significant individual prognostic factors is planned.The cumulative incidence of developing significant individual mental wellbeing outcomes during the 12-month study follow up will be calculated and presented as a percentage.To evaluate the trajectory of mental wellbeing symptoms over a 12-month period and effect of time on symptom scores, mental wellbeing outcome scores of whole cohort and individual treatment cohorts will be evaluated at each follow up time. Evaluation of these scores will be conducted using multilevel mixed-effects analyses to account for the effect of recruitment site clustering and expected loss to follow up during the study.The relationship between each individual mental wellbeing symptom and functional, social, and general health outcomes will be evaluated. Functional outcomes will include sexual, urinary and bowel symptoms from EPIC-26. Social wellbeing will include FACT-G subscale scores with general health defined using the SF-12 physical component score. All outcomes will be evaluated at 12-months. For this each mental wellbeing symptom will be continuously evaluated against these outcomes using univariable and subsequent multivariable linear regression, adjusted for known factors for functional and social outcomes.

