## Data collection and outcomes

This questionnaire-based study is conducted remotely, with no physical follow ups within a hospital site. Again, this design was selected to minimise patient risk during the COVID-19 pandemic. Recruited individuals are asked to complete a series of online or postal questionnaires depending on participant preference (S2 File). Participants are requested to complete the same questionnaire containing a battery of validated mental, physical, and social wellbeing measures at baseline, 3-, 6-, 9-, and 12-months (Fig 2). In addition, at baseline participants are requested to complete some demographic information. Reminders are sent to participants at two- and four-weeks post questionnaire dates if not received within this time frame. Participants are then assumed to be no longer interested in participation and marked as lost to follow up if not returned thereafter. Clinical data extraction is also conducted by the research team to collect baseline disease characteristics and subsequent clinical outcomes. A full list of variables to be collected and analysed as exposure/independent variables are included in Table 2. End of study participation will be at 12 months upon completion of the final questionnaire.

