**Fig 2 pone.0284727.g002:**
[figure not shown]
Study timeline.

**Table 2 pone.0284727.t002:** Exposure variables collected for subsequent prognostic evaluation during the study.

**Patient Factors**	Age at diagnosis, ethnicity, relationship/co-occupancy status, employment status, smoking status, alcohol intake, index of multiple deprivation, medical co-morbidities, current or previous mental health history, family history of mental health conditions and family history of prostate cancer
**Oncological Factors**	Gleason grade and ISUP classification, number of positive biopsy cores, risk stratification, PSA at diagnosis, TNM Score and stage classification.
**Treatment Factors**	Final treatment received, presence of positive surgical margins

Primary study outcomes collected within questionnaires included validated psychometric measures for mental wellbeing post prostate cancer diagnosis. Important mental wellbeing outcomes were defined through multiple extensive and systematic searches of the existing literature due to variable current definitions [7, 9, 10]. This selected five mental wellbeing constructs of interest which will be included within the overall primary outcome of ‘mental wellbeing’:

Depressive SymptomsAnxiety SymptomsFear of Cancer Recurrence/ProgressionBody Image PerceptionMasculine Self-Esteem

Selection of subsequent validated psychometric measures for these outcomes was based on the most utilised tools, or those with the best psychometric properties within a prostate cancer population. These were defined by previous reviews or through a dedicated review for body image and masculinity outcomes [7, 9, 21]. Final psychometric scales selected were:

Patient Health Questionnaire (PHQ)-9—Depression symptoms [22]Generalised Anxiety Disorder (GAD)-7 –Anxiety symptoms [23]Fear of Recurrence Scale 7 (FCR7)—Fear of cancer recurrence/progression [24]Body Image Scale (BIS)–Body image perception [25]Prostate Cancer-Quality of Life (PC-QOL) Masculine Self-Esteem Subset–Masculinity [26]

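### The exploratory prognostic-factor models omit the same-scale baseline score, so they cannot show whether a factor predicts significant symptoms beyond those already present at diagnosis

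*Protocol article*

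**What the plan says.** The Secondary outcomes section says that "baseline patient, oncological and treatment factors previously described will be evaluated against the binary outcome of the development of significant individual mental wellbeing symptoms" during follow-up, separately for each of the five constructs. The method is "an initial univariable, followed by a multivariable regression analysis of potentially significant individual prognostic factors is planned".

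The regressors are the patient, oncological and treatment factors described earlier. These are the three row labels of Table 2. Of that table, Data collection and outcomes says: "A full list of variables to be collected and analysed as exposure/independent variables are included in Table 2". Table 2 contains no baseline PHQ-9, GAD-7, FCR7, BIS or masculine self-esteem score. Its nearest entries are "current or previous mental health history, family history of mental health conditions and family history of prostate cancer".

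The scores are nevertheless available, because participants "complete the same questionnaire containing a battery of validated mental, physical, and social wellbeing measures at baseline" and again at each follow-up.

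The article does let EPIC-26, FACT-G and SF-12 serve as exposures in some analyses, and the fourth secondary aim uses the mental wellbeing scales as explanatory variables for 12-month function. Neither statement puts the baseline score of the outcome scale into the prognostic-factor models.

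The men at risk of developing symptoms are not defined. Under Population, the only mental health exclusion is a psychiatric inpatient admission in the 12 months before diagnosis, so men already above a threshold at baseline can enter.

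**The concern.** A man's baseline score on a scale is likely to be among the strongest predictors of his later scores on that scale. If it is left out, any factor that differs with symptoms at diagnosis inherits an association with symptoms at follow-up. Current or previous mental health history is the obvious candidate, and Study aims already hypothesises that mental health history is prognostic.

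The models then cannot tell two kinds of factor apart: those that predict later symptoms in men with the same starting level, and those that mark men who are already symptomatic. The distinction matters for the stated use. The Discussion wants factors that identify men at increased risk of developing problems and that supply candidate predictors for later prognostic models. A factor that adds nothing to a questionnaire score already recorded is of little use for the second purpose.

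There is also a question of efficiency. For a factor that is largely unrelated to the baseline score, leaving out a strong predictor of the outcome costs power.

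**Working it through.** **The plan's own figure.** There is none for these models; the article's sample size belongs to the primary ANOVA. From it I take only the number followed: 300 × (1 − 0.25) = 225.

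**Assumed inputs (not in the article).** Baseline to follow-up correlation ρ of 0.4 to 0.7; a binary factor held by 25% of men; 12% above threshold per visit, which gives about 26–30% ever above threshold over four visits.

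**Model.** Baseline score B ~ N(0,1) + d·x, where x marks factor carriers. Each of four follow-up scores = ρ·B + √(1−ρ²)·noise + e·x, with the noise variance split 40:60 between a shared and a visit-specific part. Event = any follow-up score beyond the cut. Logistic regression of the event on x alone, then on x and B, two-sided 0.05.

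**Step 1: a factor that acts only through baseline (d = 0.5, e = 0).** The expected follow-up difference is ρ × d, from 0.4 × 0.5 = 0.20 SD to 0.7 × 0.5 = 0.35 SD. Given B, it is zero. Share of studies with p<0.05, in two separate runs (800 and 1,000 replicates):

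| ρ | x alone, run 1 | x alone, run 2 |
|---|---|---|
| 0.4 | 24% | 23% |
| 0.5 | 28% | 30% |
| 0.6 | 40% | 42% |
| 0.7 | 46% | 47% |

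With B in the model the share is 4–5% (run 1) and 5–7% (run 2). With 1,000 replicates the simulation standard error near 40% is √(0.4 × 0.6 / 1000) = 1.5 points, so the runs agree. Varying d from 0.3 to 0.8 SD widens the unadjusted range to 13–85%.

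**Step 2: a different set-up.** With 17% above threshold per visit (the prevalence cited in the Introduction), a factor split 50:50 and n = 225, a 0.5 SD baseline difference gives 29%, 49% and 58% unadjusted at ρ = 0.4, 0.6 and 0.7, against 4–5% adjusted. The median odds ratio is 1.47, 1.72 and 1.86 unadjusted, and 0.99 adjusted.

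**Step 3: men above threshold at baseline excluded.** In the first set-up with d = 0.5 the unadjusted share falls to 10–16%, against 4–6% adjusted. Over d = 0.3 to 0.8 it is 7–32%. Restriction shrinks the problem but does not remove it, because sub-threshold scores still differ by factor.

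**Step 4: a factor unrelated to baseline (d = 0, e = 0.4 SD).** Power without and then with B:

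| ρ | run 1 | run 2 |
|---|---|---|
| 0.5 | 61% to 70% | 64% to 72% |
| 0.6 | 58% to 71% | 60% to 75% |
| 0.7 | 59% to 75% | 60% to 80% |

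At ρ = 0.4 the gain is about 4 points (run 2 only). Overall the gain is roughly 4–20 points.

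**Step 5: a factor correlated with baseline.** Here adjustment works the other way. If the factor drives a stable trait that the baseline score measures with error, one such model at n = 300 took detection from 95–98% unadjusted to 27–58% adjusted.

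**The case against.** The strongest reply is that the article does not fix the adjustment set. Table 2's caption speaks of exposures for prognostic evaluation, which could mean the candidates under study and not every adjuster. The article also uses variables outside Table 2 as exposures elsewhere, as with EPIC-26, FACT-G and SF-12, and with the five scales themselves in the fourth aim. Covariates of a secondary model are often left to an analysis plan.

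That shows Table 2 is not closed for every analysis. It does not reopen it for this one: the section names the three Table 2 classes as the regressors, and the article calls the table a full list.

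Two further points stand, and they limit the concern.

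- A reader might infer that the unadjusted results would be false positives. They would not. Carriers in Step 1 really do have more events, so 23–47% is the detection rate of a true crude association. The Discussion states a prognostic aim, not a causal one, and a marker of existing symptoms does identify men at higher risk. What it cannot show is value beyond the current score.
- A reader might infer that the adjusted estimate is simply the right one. The article does not support that. Baseline follows diagnosis and the multidisciplinary team's allocation of management. The exclusion criteria also admit men who have had an initial hormone injection or up to three months of tablets. Baseline symptoms may therefore already carry part of the effect of stage, risk group or treatment, and adjustment would absorb it. Which estimate to read is a choice of question.

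Mental health history in Table 2 is also a partial proxy for baseline symptoms, chiefly for depression and anxiety. The calculations give it no credit.

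**Conclusion.** The point holds in a limited form. As written, the prognostic-factor models leave out a collected baseline value and so cannot separate prediction of later symptoms from symptoms already present at diagnosis. For a factor that works only through a 0.5 SD baseline difference, the assumed inputs give p<0.05 in roughly 23–47% of studies, against about 5% with the score included. The direction is secure. The size depends on correlations, shifts and event rates that the article does not give.

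A general claim that the omission costs power would go too far. The gain of roughly 4–20 points applies to factors largely unrelated to baseline; factors correlated with it would be detected less often after adjustment.

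The analysis is secondary and declared exploratory, which limits the weight. It does not remove the point, because later studies are meant to build on the list of factors. The primary ANOVA is untouched.

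**What to change.** In Secondary outcomes, state that each multivariable prognostic model is also fitted with the continuous baseline score of the same scale forced in, exempt from univariable screening. Add the five baseline scores to Table 2.

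Report each factor's estimate without and with the baseline score, side by side. Label the first as the overall (crude) prognostic association and the second as value beyond current symptoms. Rest any claim that a factor predicts new or later symptoms on the second. Add the caveat that for stage, risk group and treatment, notably hormone therapy where baseline may follow the first dose, adjustment may absorb part of the effect.

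The cost is a change of wording, with no new data or visits. Each model spends one degree of freedom, which matters most where events are few, and the adjusted odds ratios have a narrower interpretation. Showing both estimates keeps the planned quantity available.
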